### Assessment integrity

Baseline and follow up assessments will be audio recorded. Reliability and adherence to protocol will be assessed by an independent researcher on a random sample of 20% of participants. Research officers will receive fortnightly supervision to monitor assessment, retention and blinding. The chief investigators, follow-up assessor and trial statistician will be blind to treatment group allocation.

### Sample size calculation

A total of 279 youth (93 individuals per group) will be recruited. Allowing for a 30% loss to follow-up, the trial will have 80% power and a 5% type I error to find a Cohen’s *d* of 0.5, i.e. moderate effect size. The significance level is adjusted by a factor of 2 to control the overall type I error rate at 5% for the 2 pair-wise comparisons required to test the primary hypotheses. This estimate is conservative and does not take into account the added power from adjusting for an individual’s measure at baseline or the repeated measures of the outcomes.

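### The 80% power claimed for 279 participants fits an unadjusted two-sided 5% test; at the halved significance level the protocol states, power per comparison is about 72%

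*Protocol article*

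**What the plan says.** All of this is in the Sample size calculation section of the protocol article.

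- Size: "A total of 279 youth (93 individuals per group) will be recruited".
- Attrition, power and error: "Allowing for a 30% loss to follow-up, the trial will have 80% power and a 5% type I error", for a Cohen's d of 0.5.
- Multiplicity: "The significance level is adjusted by a factor of 2 to control the overall type I error rate at 5% for the 2 pair-wise comparisons" that the primary hypotheses require (SWEL against Befriending, and SWEL against Psycho-Education).
- Margin: "This estimate is conservative and does not take into account the added power from adjusting for" the baseline measure, or from the repeated measures.

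Sidedness is not stated. The Statistical analysis section words the primary hypothesis directionally (SWEL higher at 2 months) but describes the test as one of differences between groups.

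**The concern.** The section gives a sample size, a power and a multiplicity adjustment, and the three should be consistent. Halving alpha for two comparisons raises the sample size needed for the same power, yet 93 per group is what one would obtain without halving. If so, the adjustment was described but not carried into the number.

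This is the power for the primary hypotheses. If either comparison is null, readers will take the trial to have had an 80% chance of detecting d = 0.5 when, on its own decision rule, the chance was lower. The word conservative adds to this, because it tells the reader that the true power lies above the stated figure.

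**Working it through.** **Inputs, all from the Sample size calculation section.** 93 recruited per group; 30% loss; d = 0.5; overall alpha 5%; two comparisons, so 2.5% each; no credit for baseline adjustment or repeated measures. Assumption: two-sided tests.

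**Evaluable per group.** 93 × 0.70 = 65.1, so 65.

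**Power.** For two groups of n, the noncentrality is d√(n/2) = 0.5 × √(65/2) = 2.850. The normal approximation to power is Φ(2.850 − z), where z is the two-sided critical value. The exact figure uses the noncentral t with 128 degrees of freedom.

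| Two-sided alpha per comparison | z | Normal approximation | t-test |
|---|---|---|---|
| 5% (no adjustment) | 1.960 | Φ(0.890) = 81.3% | **80.8%** |
| 2.5% (as stated) | 2.241 | Φ(0.609) = 72.9% | **71.9%** |

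The first row reproduces the protocol's 80%. The second is what its own adjustment implies.

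**Sample size, working forwards.** n = 2(z + 0.842)²/d².

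- At 5%: 2(1.960 + 0.842)²/0.25 = 62.8, so 63 (64 with the t-test). Then 64/0.70 = 91.4, so 92 per group. Starting from 65, 65/0.70 = 92.9, which is 93.
- At 2.5%: 2(2.241 + 0.842)²/0.25 = 76.0, rounded up to 77 (78 with the t-test). Then 78/0.70 = 111.4, so 112 per group and 336 in total (110 and 330 by the normal approximation).

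**Detectable effect.** With 65 per group at two-sided 2.5%, 80% power is reached at d = 0.546 (t-test) or 0.541 (normal approximation).

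**Other routes to 80% at 93 per group.**

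- Three-group pooled degrees of freedom: 72.3%.
- A Dunnett critical value (2.212): 73.8%.
- Inflating for dropout by multiplying by 1.3 instead of dividing by 0.7: 101 to 102 per group, which is not 93.
- Power for at least one of the two comparisons at 2.5%: about 86%. Power for both: about 58% by simulation with t-tests (59% by the normal approximation). Neither is 80%.
- One-sided 5% halved to one-sided 2.5%: 80.8%. This is the only variant that fits.

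**Baseline adjustment.** With a baseline-outcome correlation r, the residual SD shrinks by √(1 − r²). Power at two-sided 2.5% with 65 per group (t-test) is 76.3% for r = 0.3, 79.9% for r = 0.4 and 84.6% for r = 0.5. The protocol gives no value for r.

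**Holm's step-down test.** The smaller p-value is tested at 2.5% and, if significant, the other at 5%. I simulated three arms of 65, with SWEL better than each comparator by d = 0.5 (400,000 runs). Per-comparison power rises from 72% to about 77%, and power to win both from 58% to 69%. With no true differences, the familywise error is 4.6%.

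**The case against.** The strongest reply is sidedness. The hypothesis is directional, and a one-sided 5% level split in two gives 80.8% with 65 per group, so 93 could be correct with the adjustment applied. That is possible. However, no one-sided test is stated and the analysis is described as testing differences, so the section would still need to say so.

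Second, the planned model adjusts for baseline engagement, so actual power may be higher than 72%. This stands as a statement about the trial, and a correlation of 0.5 would take power to about 85%. It does not rescue the written figure, since the section says the gain was not counted. Eligibility also selects on low recent attendance, which narrows the baseline range and may weaken the correlation; the documents do not allow that to be quantified. Repeated measures help less. With a treatment-by-time interaction, the 2-month contrast rests almost entirely on 2-month data, and later visits contribute mainly through participants who miss month 2.

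Third, the 30% loss is not tied to a time point, and loss at 2 months may be smaller. Keeping 78 of 93 would need loss of about 16% or less (1 − 78/93 = 16.1%). The section nevertheless fixes 30%.

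Fourth, the 58% for winning both should not be pressed. The protocol does not clearly set a both-must-win rule, and under such a rule each test could be run at 5%, with joint power of about 70%.

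Finally, Bonferroni is valid. Holm is an improvement, and the correction does not depend on it.

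**Conclusion.** The concern holds. As written, the section's power is wrong for its stated significance level: 71.9% per comparison, not 80%, so the type II error is 28% rather than 20%. The number 93 matches an unadjusted two-sided 5% test.

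The conclusion assumes two-sided testing and takes the section's own 30% loss, d = 0.5 and exclusion of baseline gains at face value. What the trial will achieve in practice is unknown and could reach 80% if the baseline correlation is about 0.40 or more. As a description of the stated figure, conservative is wrong, because the uncounted gain must first make up a shortfall of about 8 points. Neither the type I error nor the treatment estimate is affected.

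**What to change.** In the Sample size calculation section:

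1. State that the tests are two-sided and that each comparison is made at 2.5%. If one-sided tests were intended, say so there and in the Statistical analysis section.
2. Restate the power. With 93 per group and 30% loss, it is about 72% for d = 0.5, or 80% for d of about 0.55.
3. Delete the word conservative, or state and justify the baseline-outcome correlation (about 0.40 or more) on which 80% would depend.

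As an optional gain, name Holm's step-down procedure for the two primary comparisons in place of simple halving. It keeps the 5% familywise error and raises per-comparison power to about 77%.

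The cost is wording in two sections and a less favourable stated power. No participants are added. Keeping 80% at d = 0.5 under simple halving, without relying on baseline adjustment, would instead mean 336 participants, which is 57 more than the 279 planned.

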### Statistical analysis

The primary outcome of this study will be engagement in education, training or employment (Time-Use Questionnaire) at the 2 month time point. Secondary outcomes include the Time-Use Questionnaire at 8 and 14 months, as well as social activity, quality of life and relationship quality (SFS), perceived social self-efficacy (Perceived Empathic and Social Efficacy Scale), sense of self (Rosenberg Self-Esteem Scale), and functioning (SOFAS, GF: Social, GF- Role, SFS, MAFS), measured at baseline, end of treatment (2 months) and at 6 and 12 months post treatment.

The primary hypothesis is that the overall engagement score (calculated as actual/expected engagement in school/work/training) of youth who are randomised to active treatment (SWEL) will be higher than those randomised to either Befriending or Psycho-Education at the 2 month time point. Differences between treatment groups will be tested within a Linear Mixed Model (LMM). The outcome in the model will be individual total engagement scores at each post treatment time point and the predictor variables in the model will include treatment group, time, the interaction between treatment group and time, baseline engagement score and the stratifying variables. The model will include a random intercept term to control for the repeated measurements on individuals. All analyses will be based on the intention to treat principle. Differences between groups in all secondary outcomes will be tested using the same approach as outlined for the primary outcome variable. Additional LMM will be used to test for a difference between treatment groups in the trend of each of these outcomes from baseline to 12 months post-treatment using data from all time points. Subgroup analyses will be conducted to examine the similarity of the treatment effect across age groups.

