## Methods

### Study design

The trial is a single blind three arm randomised controlled trial evaluating the effectiveness of a telephone-delivered social well-being and engaged living (SWEL) intervention for improving the vocational, social and emotional functioning of disengaged youth. Participants will be randomised to receive either (i) SWEL, (ii) Befriending, or (iii) Single Session Psycho-Education. Befriending has been applied in a RCT of CBT for youth with a first episode of psychosis [27] and has been developed in earlier clinical trials to address the nonspecific elements of psychotherapy [28]. Outcomes will be assessed at baseline and at 2, 8 and 14-month follow-up, with assessments conducted over the phone and online. Figure 1 provides an overview of the trial participant flow. Design and implementation is being carried out with the ongoing direct input from our Aboriginal communities.

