##### Engagement

A Comprehensive Time-Use Questionnaire of 28 items with skip logic measures the level of engagement in education, training, employment and seeking work since the last follow-up. Items include type of education attended (e.g. school, certificate, etc.), number of hours attended and length of enrolment in the program. The items for training, employment, job searching and volunteer work follow the same pattern.

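### A random intercept as the only covariance term gives the primary 2-month contrast a standard error pooled over three visits, which is mis-scaled if the visit variances differ

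*Protocol article*

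**What the plan says.** All points below are from the protocol article.

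- **Primary endpoint** (Statistical analysis): "engagement in education, training or employment (Time-Use Questionnaire) at the 2 month time point". The score is a ratio, "calculated as actual/expected engagement in school/work/training".
- **Data in the model** (Statistical analysis): "The outcome in the model will be individual total engagement scores at each post treatment time point". The 2-, 8- and 14-month scores are therefore fitted together.
- **Mean structure** (Statistical analysis): treatment group, time, "the interaction between treatment group and time, baseline engagement score and the stratifying variables". The 2-month contrast is thus specific to that visit.
- **Covariance** (Statistical analysis): "The model will include a random intercept term to control for the repeated measurements on individuals". Nothing further is said about residual variance, and the secondary outcomes are to be analysed in the same way.
- **Timing** (Study design): "Outcomes will be assessed at baseline and at 2, 8 and 14-month follow-up".
- **Recall window** (Engagement, under Baseline and follow-up measures): the Comprehensive Time-Use Questionnaire "measures the level of engagement in education, training, employment and seeking work since the last follow-up".
- **Error rate** (Sample size calculation): the significance level is halved so that the two pairwise comparisons together keep the type I error at 5%.

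**The concern.** A random intercept with independent, equal-variance residuals implies the same total variance at every visit. The trial's decision is taken at one visit, 2 months. Because group-by-time is in the model, the estimated contrast is the 2-month difference, but the variance behind its standard error is borrowed from all three visits. If engagement is more variable at 2 months than later, the test is too liberal and the halved significance level no longer delivers the control it was chosen for. If engagement is less variable at 2 months, the test is too conservative and power is lost.

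Two features of the design make equal variances doubtful, and they pull in opposite directions:

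- **Recall window.** If the score covers the period since the last follow-up, the windows are about 2, 6 and 6 months. A ratio over a short window is generally noisier, which would raise the 2-month variance.
- **Entry selection.** The Engagement screener admits only young people with under two thirds attendance over the last 3 months and excludes those with none over 6 months. Scores start in a restricted range and may spread as some participants re-engage and others do not. That would raise the later variances.

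**Working it through.** **Inputs**

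- Visits at 2, 8 and 14 months (Study design). The windows since the previous assessment are 2 − 0 = 2, 8 − 2 = 6 and 14 − 8 = 6 months.
- Per-comparison level 5% / 2 = 2.5% (Sample size calculation). Sidedness is not stated; two-sided is assumed here, so the critical value is 2.241.
- 93 per arm with 30% loss (Sample size calculation): 93 × 0.70 = 65 evaluable.
- SDs by visit and correlations between visits are not given. Every SD set below is an assumption and stands for the SD after adjustment for baseline and the stratifying variables.

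The article states no standard error or SD for this analysis, so there is no figure of its own to reproduce. The benchmark is the 2.5%.

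**Step 1: standard error of the 2-month contrast, complete data, n per arm**

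- Random-intercept model: SE_model = sqrt(2·v/n), where v = (s2² + s8² + s14²)/3.
- Correct value: SE_true = sqrt(2·s2²/n).
- Ratio R = SE_model / SE_true = sqrt(v / s2²). Sample size cancels.

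**Step 2: actual error per comparison** = 2·(1 − Φ(2.241·R))

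| SDs at 2/8/14 months (assumed) | v | R | Actual error |
|---|---|---|---|
| 0.40/0.30/0.30 | (0.1600 + 0.0900 + 0.0900)/3 = 0.1133 | 0.842 | 5.9% |
| 0.35/0.30/0.30 | (0.1225 + 0.0900 + 0.0900)/3 = 0.1008 | 0.907 | 4.2% |
| all equal | s2² | 1.000 | 2.5% |
| 0.30/0.40/0.40 | (0.0900 + 0.1600 + 0.1600)/3 = 0.1367 | 1.232 | 0.6% |

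On a relative scale, SDs of 1/0.8/0.8 give R = sqrt(0.76) = 0.872 and an error of 5.1%. SDs of 0.8/1/1 give R = sqrt(0.88)/0.8 = 1.173 and an error of 0.9%.

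**Step 3: power in the conservative direction.** Take SDs 0.8/1/1 and a difference of 0.5 × 0.8 = 0.4. With 93 per arm, SE_true = 0.8·sqrt(2/93) = 0.1173 and SE_model = sqrt(0.88·2/93) = 0.1376.

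- Random intercept: Φ((0.4 − 2.241 × 0.1376)/0.1173) = Φ(0.78) = 0.78.
- Correct variance: Φ(0.4/0.1173 − 2.241) = Φ(1.17) = 0.88.
- With 65 per arm the same calculation gives 0.59 against 0.73.

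**Step 4: check with dropout.** Random-intercept models were fitted by REML to simulated data with 93 per arm and assumed monotone loss of 10/20/30% (400 runs, Monte Carlo error about 1 percentage point):

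- SDs 1/0.8/0.8: empirical SE 0.157, mean model SE 0.136, error 4.5% (formula extended to this loss pattern: 4.8%).
- SDs 0.8/1/1: empirical SE 0.132, mean model SE 0.143, error 1.3%.
- Equal SDs: empirical SE 0.150, mean model SE 0.154, error 3.3%, about one Monte Carlo error from the nominal 2.5%.

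**Step 5: is it the variance or the correlation?** With equal SDs and a correlation that falls with the gap between visits, the SE ratio stays at 1.00 and the error at 2.5%. The harm comes from the single variance.

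**The case against.** The strongest reply is that the harmful assumption is not written down. A random intercept is compatible with visit-specific residual variances or robust standard errors, and an analysis plan that is not shown may add either. This stands as a limit on certainty. It does not remove the point: the article chooses to name a covariance device, names only this one, and on the usual reading that device constrains the variance.

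A second reply is that the article gives no SDs, so the size and even the sign of the error are unknown. This stands in full. The 5.9% case is near the severe end. Suppose months are exchangeable within a person with correlation ρ, before baseline adjustment. The variance of an m-month average is then proportional to ρ + (1 − ρ)/m. An SD ratio of 0.40 to 0.30 needs ρ of about 0.21. At ρ = 0.5 the 2-month to 6-month variance ratio is 0.750/0.583 = 1.286 and the error is 3.9%; at ρ = 0.7 it is 0.850/0.750 = 1.133 and the error is 3.1%. Baseline adjustment would remove some persistent variance and raise these figures, so they are not a bound. The Statistical analysis section also does not say which period the ratio score covers; the 2, 6 and 6 months are inferred from the questionnaire.

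A reader might go on to infer three stronger things that the document does not support:

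- **That correlation falling over time distorts this standard error.** Step 5 shows almost no effect.
- **That the single baseline slope invalidates the contrast.** Under randomisation it mainly affects precision, and no harm has been quantified.
- **That the loss comes on top of a trial already short of its stated power.** That is a separate sample-size question which turns on the unstated sidedness, and nothing here depends on it.

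**Conclusion.** The point holds in conditional form. As the article describes the model, and with the usual equal-variance residuals, the standard error of the primary 2-month contrast is mis-scaled by sqrt(mean of the three variances / 2-month variance) whenever the visit variances differ. Over the assumed SD sets, the actual per-comparison error runs from about 0.6% to about 5.9% against a nominal 2.5%, and equal variances do no harm. The design makes differing variances plausible but does not settle the direction, so a reader should not conclude that the type I error is inflated. With complete data the estimated difference is unbiased; the fault lies in its standard error and test. The conditional algebra is secure, whereas the magnitudes are illustrations. The change is worth making because it protects the error control promised in the Sample size calculation section at almost no cost.

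**What to change.** In Statistical analysis, replace the random-intercept sentence with an unstructured covariance over the three post-baseline visits, with time as a categorical factor, REML estimation and Kenward-Roger degrees of freedom. Take the SWEL versus Befriending and SWEL versus Psycho-Education contrasts at 2 months from that model. If the random intercept is to be kept, the minimum is to allow a separate residual variance at each visit. A baseline-by-time term is an optional refinement.

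The cost is one sentence and six covariance parameters in place of two, that is four more, with roughly 195 (3 × 65) to 279 participants to estimate them. In the calculations above, the 2-month standard error then equals its true value and the error returns to 2.5% per comparison in every scenario. Because the secondary outcomes follow the same approach, the change carries over to them.

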### Trial duration

July 2014 – June 2018.

### Ethics and dissemination

Safety and risk management protocols were devised to manage safety or urgent treatment issues. Young people recruited to this study and subsequently identified as needing more intensive treatment will be appropriately referred. A clinical committee comprised of LH, AB, the project manager, research clinicians and follow-up researchers will meet fortnightly to resolve treatment difficulties and discuss any departures from the protocol. The authors will meet quarterly to monitor the study’s implementation, clinical and research integrity. The informed consent of young people will be obtained by recruitment staff and parental or guardian consent for people aged 12–15 years will be sought.

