SWEL research clinical psychologists will contact new participants within 24 h of receiving referrals. They will provide detailed information about the trial, obtain consent verbal and confirm eligibility. A 20–30 min baseline assessment will be conducted by phone immediately after screening. During this assessment participant age, gender, ethnicity and location will be recorded. Thereafter participants will complete online versions of self-report measures. Reporting will follow the CONSORT guidelines (Fig. 1) [30]. Follow-up assessments consisting of an online survey and telephone interview will be conducted at 2, 8, and 14 months post-baseline by research officers blinded to treatment allocation. To enhance retention, participants will be emailed a link to the online survey 1 day before, then one and 3 days after the follow-up is due. In order to ensure that participants have received the survey link, it will also be sent via a SMS 2 days after the online survey is due. Participants will receive $AUD40 cash for each assessment time point (total $AUD160) to encourage engagement and follow-up completion. Those who have not responded to the initial calls will be contacted on a weekly basis by phone and SMS for up to 4 weeks after follow-up is due.

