### Psychological interventions

Research therapists will complete a one-day training workshop [led by HS and/or LH] for the SWEL, Befriending and Single Session Psycho-Education conditions. An Aboriginal Youth Worker will be available to support the research therapists and the Aboriginal participants with treatment engagement, attendance and delivery. All interventions will be delivered by telephone and participants will be reimbursed $AUD10 cash per session to maximise retention and treatment completion. Participants in the SWEL and Befriending conditions will initially be encouraged to participate in at least four sessions. Once engaged they will be offered four additional sessions, receiving a maximum of eight (one per week). Participants randomised to Psycho-Education will receive one session over the eight-week period. Sessions are 30–60 min duration and will be audio-recorded. Therapists will ensure participants are in an appropriate setting during therapy calls to maintain participant privacy and confidentiality.

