#### Befriending intervention

Befriending is a manualised intervention developed in earlier clinical trials to address the non-specific elements of psychotherapy [47]. It controls for therapist contact time, client expectancies, therapeutic alliance and therapist factors (e.g., warmth and understanding) and has been used in a randomised controlled trial of CBT for youth with a first episode of psychosis [28]. It does not apply therapeutic techniques specific to major models of psychotherapy and focuses on everyday events and topics using a conversational, friendly approach, without problem solving or examination of emotions. Befriending will be delivered for up to eight weekly sessions to allow for the same level of contact as the SWEL condition.

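### Follow-up researchers sit on the fortnightly clinical committee with the clinicians, which puts the stated blinding of follow-up assessors at risk

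*Protocol article*

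**What the plan says.** Study design describes the masking level: "The trial is a single blind three arm randomised controlled trial". Two sections then say who is blind. Under Recruitment and follow up procedures, the follow-up assessments "will be conducted at 2, 8, and 14 months post-baseline by research officers blinded to treatment allocation". Under Assessment integrity, "The chief investigators, follow-up assessor and trial statistician will be blind to treatment group allocation". The same section gives one safeguard: "Research officers will receive fortnightly supervision to monitor assessment, retention and blinding".

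Ethics and dissemination describes a clinical committee made up of two people given by initials, the project manager, the research clinicians and the follow-up researchers. Its remit is that these "research clinicians and follow-up researchers will meet fortnightly to resolve treatment difficulties and discuss any departures from the protocol". The article gives no rule for how allocation is kept from the follow-up researchers at that meeting.

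**The concern.** The article promises that those who collect follow-up data do not know the arm. It then makes follow-up researchers regular members of the meeting at which problems with treatment are worked through, beside clinicians who know what each participant receives. If the plan is followed as written, the assessors' blinding depends on what happens to be said at each meeting.

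At stake is the credibility of assessor masking in a trial that compares psychological treatments. Follow-up has an online survey and a telephone interview, so an assessor who has learned the arm is in direct contact with the participant while outcome data are gathered. Expectations about an arm could then affect how questions are put or answers recorded.

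**Working it through.** The plan gives no figure on this point, so the check compares its statements.

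1. **Are they the same staff?** The article uses three terms: research officers (Recruitment and follow up procedures; Assessment integrity), follow-up assessor (Assessment integrity) and follow-up researchers (Ethics and dissemination). It describes no second, unblinded follow-up team. That all three terms mean the same people is the natural reading, though it is not stated. Likewise, Psychological interventions calls those who deliver treatment research therapists, and taking the committee's research clinicians to include them is natural given its remit.

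2. **Can a discussion of treatment reveal the arm?**
   - *Session number.* In Psychological interventions, SWEL and Befriending aim for at least four sessions and allow at most eight. By contrast, "Participants randomised to Psycho-Education will receive one session over the eight-week period". Any mention of a second or later session, or of missed weekly calls, rules out Psycho-Education.
   - *Content.* The SWEL core modules include goal setting, emotion regulation and behavioural activation, and problem solving is an optional module. Befriending is delivered "without problem solving or examination of emotions". A difficulty with a module or a technique points to SWEL.
   - A departure from protocol in treatment delivery is hard to describe without one of these two features.

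3. **Does this happen before the primary assessment?** Treatment runs over 8 weeks and the primary outcome is taken at 2 months. A meeting every 2 weeks gives 8 / 2 = 4 meetings, so about four during one participant's treatment period. What an assessor learns there can also carry over to the 8- and 14-month follow-ups.

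4. **Does the stated safeguard cover it?** The fortnightly supervision of research officers covers assessment, retention and blinding. It is described apart from the committee, and nothing in it keeps officers out of the committee's discussion. Masked case presentation, a split agenda or withdrawal from case discussion is not mentioned.

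The blinding statements and the committee's membership and remit therefore pull against each other, and nothing in the article reconciles them.

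**The case against.** The strongest reply is that the conflict is inferred. The article does not say that allocation is disclosed at the committee, or that cases are discussed one by one. Meeting procedure is the kind of detail an article leaves to the full protocol, and blinding is said to be monitored. Part of this stands: the finding is a risk, and a masking procedure may exist elsewhere. It does not remove the point, because the tension lies between rules that the article itself states, and the supervision it describes does not extend to this committee.

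Several stronger readings are tempting, and the document does not support them:

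- *That the assessors will be unblinded.* This needs disclosure at the meetings, which is not stated. Only participants whose treatment or departures are discussed could be affected.
- *That the false-positive rate rises by a given amount.* This needs a size of rater bias and the share of participants exposed. The article gives neither.
- *That the assessor is the only blinded party.* Assessment integrity also blinds the chief investigators and the trial statistician.
- *That chief investigators are shown to be unblinded.* The text provided does not say whether the two members given by initials are chief investigators.
- *That SOFAS and the two Global Functioning scales are rated by the interviewer.* The Functioning section calls MAFS self-report and names no rater for these three. All three are secondary outcomes.
- *That the primary outcome is directly biased.* It comes from the Time-Use Questionnaire. Measures are completed online or by telephone, and the article does not say which part of follow-up carries this one.

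**Conclusion.** The concern holds as a risk. Assessors stated to be blind are, on the natural reading, members of a fortnightly meeting on treatment problems with clinicians who know the arms. The arms can be told apart by session number and content, and the meetings fall before the 2-month primary assessment. The conclusion assumes that the three terms for follow-up staff mean the same people and that the committee discusses treatment in enough detail to show session number or content. How many participants would be affected, and by how much assessments would shift, cannot be estimated from the document. The statements need to be reconciled, because the plan as written does not protect the blinding it promises.

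**What to change.** - In Ethics and dissemination, take the follow-up researchers out of the committee's discussion of treatment and departures. They already have separate fortnightly supervision under Assessment integrity. Alternatively, let them attend only a masked part of the agenda and state how allocation is hidden there.
- Let issues raised by assessors pass to the committee one way, with no treatment information coming back to them.
- Use one term for the follow-up staff throughout, so that it is clear who is blind.
- If any chief investigator sits on the committee, amend the blinding statement in Assessment integrity to say so.

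The cost is small: a changed membership or split meeting, one added relay step, and a few sentences in the protocol.
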